### 2.7. Ethical Issues

Procedures will be performed in accordance with the ethical standards described in the Declaration of Helsinki as revised in 2013, and the study protocol has been approved by national regulatory agencies and the Ethical Review Board of the Vall d’Hebron University Hospital with the reference number EOM(AG)008/2021(5790). Written informed consent will be obtained from all participants.

## 3. Discussion

Human strongyloidiasis is still a challenging disease not only in endemic countries, but also in nonendemic countries due to the migration fluxes. Ivermectin has proved to be an effective drug in eliminating the infection, but easier treatment schemes are needed to optimize control strategies and diagnose as much of the infected population as possible [2]. In this regard, the Strong Treat clinical trial has shown high cure rates with a single-dose ivermectin treatment in immunocompetent patients with uncomplicated strongyloidiasis [14]. The ImmunoStrong study aims to continue evaluating the efficacy of a single-dose ivermectin strategy for uncomplicated strongyloidiasis, placing the focus on immunosuppressed patients. 

Information about efficacy of ivermectin for strongyloidiasis in immunosuppressed patients is scarce, since most of the clinical trials have been carried out in immunocompetent patients [12]. Information about treatment efficacy in immunosuppressed patients comes from case series, where patients are usually treated with similar treatment schemes as immunocompetent patients unless they present a severe clinical form. In the absence of disseminated strongyloidiasis or *S. stercoralis* hyperinfection syndrome, efficacy seems to be the same in both groups [17]. The ImmunoStrong study will raise relevant information to optimize treatment schemes in immunosuppressed patients.

The single-dose ivermectin scheme for the treatment of strongyloidiasis opens a range of possibilities and opportunities for the strongyloidiasis control strategies. If this treatment scheme demonstrates efficacy in both groups (immunocompetent and immunosuppressed), it would facilitate mass drug administration campaigns in highly endemic areas. This strategy is already being evaluated by the WHO in pilot studies [2]. A recent study evaluating different strategies of imported strongyloidiasis screening and treatment showed that presumptively treating all immunosuppressed migrants from endemic areas is the most cost-effective strategy [18]. If the efficacy of a single-dose ivermectin scheme is demonstrated in this population, this strategy will become even more affordable. 

The strongyloidiasis diagnosis and follow-up in the ImmunoStrong study is mainly based on serological techniques, which is closer to real-life conditions. Some concerns could arise regarding the sensitivity of serological techniques in immunosuppressed patients, and this fact could affect the patients’ recruitment of the IS group. Regarding specificity issues of the serological techniques, it has been suggested that increasing the cut-off value for positive serology may increase the specificity of the serological test in the diagnosis of confirmed strongyloidiasis [19]. For this reason, patients included in the ImmunoStrong study must have an OD index equal to or greater than 2 in the ELISA test at the time of diagnosis in the absence of larvae detection in parasitological techniques. 

Novel molecular-based diagnostic techniques for strongyloidiasis diagnosis have been developed in the last decades to achieve the highest sensitivity and specificity. A recent meta-analysis, which included 14 studies, evaluated the accuracy of molecular biology techniques for the diagnosis of *S. stercoralis* infection, showing very high specificity of the PCR technique. However, sensitivity showed unsatisfactory results regardless of the reference test used [20]. Moreover, among the 14 included studies, only 1 was performed in immunosuppressed patients, showing scarce benefits of PCR techniques compared with classical parasitological techniques in patients with oncologic diseases [21]. This gap of information will also be covered by the ImmunoStrong study, which will compare the PCR technique with classical parasitological techniques and serology for the strongyloidiasis diagnosis and follow-up after treatment, both in immunocompetent and immunosuppressed patients.

Finally, the present study will perform an ivermectin population pharmacokinetics among the included patients. The information of this sub-study among immunosuppressed patients could be crucial, since this population is usually under a broad range of treatments that could affect the ivermectin concentrations in blood, subsequently affecting the potential efficacy of the single-dose strategy. 

Concluding, the ImmunoStrong study will focus on the strongyloidiasis treatment among immunosuppressed patients, aiming to find an effective and easier method to implement the treatment scheme based on ivermectin. Information about the accuracy of the PCR technique for the diagnosis and follow-up of these patients and the ivermectin population pharmacokinetics will also fill information gaps in this kind of population.

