## Abstract

Strongyloidiasis affects an estimated 600 million people worldwide, especially in tropical and subtropical areas. Single-dose ivermectin treatment has shown to be effective among immunocompetent patients with uncomplicated strongyloidiasis. Here, we present the protocol of the ImmunoStrong study, a prospective observational study aiming to evaluate the effectiveness and safety of a single-dose ivermectin for treatment of uncomplicated strongyloidiasis in immunosuppressed patients. The secondary objectives are to assess accuracy of molecular techniques for the follow-up of these patients and to determine the population pharmacokinetics of ivermectin. The information retrieved by this study will cover relevant information gaps in the strongyloidiasis management among immunosuppressed patients.

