## 2. Methods

The ImmunoStrong Study is a prospective observational study where adult immunosuppressed (IS) patients with uncomplicated strongyloidiasis will be included. Control group will be composed by immunocompetent (IC) patients with uncomplicated strongyloidiasis. The study will be carried out in 8 sites in Spain and Italy: Vall d’Hebron University Hospital (Barcelona, Spain), Germans Trias I Pujol University Hospital (Badalona, Spain), Ramón y Cajal University Hospital (Madrid, Spain), La Paz-Carlos III University Hospital (Madrid, Spain), 12 de Octubre University Hospital (Madrid, Spain), Vega Baja Hospital (Orihuela, Spain), General University Hospital of Valencia (Valencia, Spain), and IRCCS Ospedale Sacro Cuore-Don Calabria (Negrar, Italia). The Parasitology Reference and Research Laboratory of the National Microbiology Center of the Carlos III Health Institute (ISCIII, Madrid, Spain) will perform the molecular diagnosis techniques.

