### 2.1. Patient Eligibility

Inclusion criteria will include: Adult patients (≥18 years old) who sign the informed consent, diagnosis of strongyloidiasis either by direct parasitological methods (positive coproparasitological examination and/or agar plate culture) or by positivity of a serological technique (ELISA) with an optical density (OD) index greater than or equal to 2, and current residence in an area without evidence of active transmission of strongyloidiasis. The exclusion criteria will be as follows: Pregnancy or lactation, intolerance or allergy to ivermectin, renal failure (glomerular filtration rate equal to or less than 30 mL/min) or advanced liver disease (Child-Pugh B or C), coinfection by *Loa loa* (due to the risk of presenting encephalopathy when administering ivermectin), complicated strongyloidiasis (*S. stercoralis* hyperinfection syndrome or disseminated strongyloidiasis), planned trip to an area with evidence of active transmission of strongyloidiasis during the next 6 months (to avoid possible reinfections), and previous treatment with ivermectin (in the last year before inclusion).

Patients included in the IS group will be defined by presence of any of the following conditions at enrollment: Treatment with corticosteroids at a cumulative dose greater than or equal to 20 mg/day of prednisone (or equivalent) for at least 10 days, treatment with cytotoxics drugs or antimetabolites, bone marrow or solid organ transplantation, biological drugs, active solid or hematological neoplasia, HIV infection with CD4 lymphocyte count below 200 cells/mm^3^. On the other hand, patients included in the IC group must not have any of the previous conditions (and no HIV infection regardless of the CD4 lymphocyte count).

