### 2.2. Outcomes

The primary outcome will be noninferiority of the cure rate of immunosuppressed patients compared to immunocompetent patients. Cure rate is defined as the proportion of patients with a negative direct parasitological test and negative *S. stercoralis* serology or decrease of at least 50% of OD index at 6 months after treatment administration. We used a noninferiority margin of 14% to assess the primary outcome (i.e., lower bound of the 1-sided 95% CI of the difference between cure rates in immunosuppressed versus immunocompetent patients was no more than –14%). The secondary objective will be to compare the safety and tolerability of single dose ivermectin for the treatment of uncomplicated strongyloidiasis between immunosuppressed and immunocompetent patients. Three sub-studies have been prespecified: Evaluation of the usefulness of *S. stercoralis* PCR in feces in the follow-up after treatment of uncomplicated strongyloidiasis in adult patients (proportion of patients with negative *S. stercoralis* PCR after treatment compared to proportion of patients that fulfill the cure criteria),Determination of the population pharmacokinetics (PK) of ivermectin in a single dose for the treatment of uncomplicated strongyloidiasis in adult patients, andCreation of a repository of serum and stool samples from adult patients (immunosuppressed and immunocompetent) with uncomplicated strongyloidiasis (samples before and after treatment with ivermectin) for later use in the evaluation of new diagnostic tools or biomarkers.

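### The Discussion promises PCR accuracy for diagnosis, but entry requires a positive stool test or serology: specificity cannot be estimated, and PCR's sensitivity relative to those tests is biased downwards

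*Protocol article*

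**What the plan says.** Two sentences in section 3 (Discussion) make the diagnostic claim. One describes a study "which will compare the PCR technique with classical parasitological techniques and serology for the strongyloidiasis diagnosis and follow-up after treatment", in immunocompetent (IC) and immunosuppressed (IS) patients. The closing paragraph adds that "Information about the accuracy of the PCR technique for the diagnosis and follow-up of these patients" will fill gaps.

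The stated aims are narrower. The Abstract's objective is to "assess accuracy of molecular techniques for the follow-up of these patients". The sub-study in section 2.2 concerns "PCR in feces in the follow-up after treatment of uncomplicated strongyloidiasis in adult patients".

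Entry under section 2.1 requires "diagnosis of strongyloidiasis either by direct parasitological methods (positive coproparasitological examination and/or agar plate culture) or by positivity of a serological technique (ELISA") with an OD index of 2 or more. The Discussion repeats that patients "must have an OD index equal to or greater than 2 in the ELISA test at the time of diagnosis in the absence of larvae" being found. PCR is not a route of entry. The comparison group is infected too: "Control group will be composed by immunocompetent (IC) patients with uncomplicated strongyloidiasis" (section 2).

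Section 2.3 requires stool study, culture and serology in all patients at baseline, and Table 1 schedules PCR at screening. All four results should therefore exist for each enrolled patient.

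**The concern.** Diagnostic accuracy needs people without the infection, for specificity, and a set of infected people whose inclusion did not depend on the tests being compared. This cohort has neither. Stool and serology decide who enters, and PCR does not. An infected patient found only by stool, or only by serology, is counted. An infected patient found only by PCR never appears.

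The Discussion presents the study as covering a gap left by a single earlier study in immunosuppressed patients, which found little benefit of PCR over classical stool methods. A baseline comparison across all entrants would be tilted in that same direction by the entry rule. A reader could not separate the tilt from a real finding.

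**Working it through.** **The plan's own figure.** No sensitivity, specificity or sample size is given for the PCR comparison. The only figure to reproduce is the sample size in section 2.6, which sets the cohort: 85% cure in both groups, margin 14%, one-sided 5%, power 80%.

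n = (1.645 + 0.842)² × 2 × 0.85 × 0.15 / 0.14² = 80.4, so 81 per group. 81 / 0.9 = 90 per group, 180 in total. This agrees with the plan.

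**Specificity.** Of the 180 patients, the number negative on both entry criteria at baseline is 0 by rule. Stool-negative entrants do not serve as disease-free controls, because they entered as seropositive.

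**Relative sensitivity.** Among infected patients, let s, e and p be the sensitivities of stool methods, serology at OD index ≥2, and PCR. Every stool-positive or serology-positive infected patient meets the diagnostic criterion, so among entrants:

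- apparent stool sensitivity = s / P(entry)
- apparent serology sensitivity = e / P(entry)
- apparent PCR sensitivity = p × P(entry | PCR+) / P(entry)

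Hence observed PCR:stool ratio = (p/s) × P(entry | PCR+), and observed PCR:serology ratio = (p/e) × P(entry | PCR+). The factor cannot exceed 1, whatever the sensitivities or the dependence between tests.

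**Size, under assumptions.** Take serology as independent of the two stool-based tests and let PCR and stool have correlation ρ:

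- P(stool+, PCR+) = sp + ρ√[s(1−s)p(1−p)], capped at its largest possible value
- shortfall = 1 − P(entry | PCR+) = (1−e) × P(stool− | PCR+)

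With p = 0.60, the shortfall in the ratio at ρ = 0 / 0.3 / 0.6 is:

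| Stool s | e = 0.9 | e = 0.7 | e = 0.5 |
|---|---|---|---|
| 0.3 | 7.0 / 5.9 / 5.0% | 21.0 / 17.6 / 15.0% | 35.0 / 29.4 / 25.0% |
| 0.5 | 5.0 / 3.8 / 2.6% | 15.0 / 11.3 / 7.7% | 25.0 / 18.9 / 12.8% |
| 0.7 | 3.0 / 1.9 / 0.8% | 9.0 / 5.6 / 2.3% | 15.0 / 9.4 / 3.8% |

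At s = 0.3 and ρ = 0.6 the cap applies: every stool-positive patient is PCR-positive.

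**Can the ranking change?** Take s = 0.5 and p = 0.6, a true ratio of 1.20.

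- At ρ = 0 the observed ratio is 1.14 (e = 0.9), 1.02 (e = 0.7) and 0.90 (e = 0.5). Only the last reverses.
- At e = 0.5 and ρ = 0.6 it is 1.05, with no reversal.
- At e = 0.6, P(entry) = 1 − 0.5 × 0.4 = 0.80 and stool appears as 0.5/0.80 = 62.5%. PCR appears as 60.0% at ρ = 0, 63.7% at ρ = 0.3 and 67.3% at ρ = 0.6. The reversal disappears above ρ of about 0.20.

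**IS against IC** (p = 0.6, ρ = 0.3). With s = 0.4 in both groups, the shortfall is 4.8% at e = 0.9 and 14.4% at e = 0.7, so it is larger where serology is weaker. If stool detection were higher in IS patients (s = 0.8, e = 0.7), it would be 3.1%, less than the 4.8% for IC at s = 0.4 and e = 0.9.

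**The case against.** The strongest reply is that this concerns Discussion wording and not a planned analysis. The Abstract and section 2.2 confine the PCR aim to follow-up, and no outcome or sample size rests on baseline diagnosis. The first Discussion sentence promises only a comparison, which the baseline data allow; only the closing paragraph speaks of accuracy for diagnosis. The same section reports that specificity is already known to be very high, so the open question is sensitivity. PCR positivity among stool-positive patients is not distorted, since all of them meet the diagnostic criterion. Details of a baseline analysis may also sit in a document not shown.

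Much of this stands, and it limits the weight of the point. It does not remove it: no analysis plan can recover patients whom the entry rule keeps out, and a comparison across all entrants is tilted against PCR in a known direction.

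Three stronger readings are tempting and not supported:

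- **That the bias is greatest in immunosuppressed patients.** The Discussion says only that "Some concerns could arise regarding the sensitivity of serological techniques in immunosuppressed patients", without a figure. The Introduction says immunosuppression can amplify autoinfection, which could raise stool detection and reverse the order, as the last calculation shows.
- **That the design guarantees a finding of little PCR benefit, or makes PCR look worse than stool methods.** That needs low serology sensitivity and low PCR–stool correlation together. Both tests look for the same parasite in stool, so positive correlation is the natural case.
- **That PCR's own sensitivity is understated.** The bias is relative to the comparators. With ρ above 0, PCR's apparent sensitivity among entrants rises from 60% to between 61% and 70% in the scenarios above.

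**Conclusion.** The point holds as a mismatch between a stated claim and the design. Two parts need no assumed figure: diagnostic specificity cannot be estimated, and the PCR:stool and PCR:serology sensitivity ratios across all entrants cannot exceed, and will generally fall below, their true values. The size, about 1–35%, is illustrative. It rests on assumed sensitivities, on serology being independent of the stool-based tests, and on the chosen range of correlation. A change of rank between PCR and stool methods is possible but not implied. A larger bias in IS patients is possible if serology is weaker there, but the documents do not establish it. The primary noninferiority outcome is untouched. The claim should be corrected before baseline PCR results are reported.

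**What to change.** 1. In the Discussion and its closing paragraph, limit the PCR claim to follow-up and to relative detection at baseline among enrolled patients.
2. Make the baseline comparison of PCR with stool examination or culture a paired one (McNemar), restricted to patients with OD index of at least 2, and report it separately for IS and IC. These patients meet the diagnostic criterion whatever their stool and PCR results, so selection favours neither test.
3. In patients who entered on stool alone, report PCR positivity descriptively.
4. State that specificity, and sensitivity relative to serology, cannot be estimated from this cohort.

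The cost is wording and one restricted analysis of data already scheduled in section 2.3 and Table 1. The price is a narrower claim, and stool-positive patients with OD index below 2 leave the paired comparison. Keeping the claim of accuracy for diagnosis would instead require a consecutive cohort of suspected cases that includes patients negative on both entry tests, which is a different and larger undertaking.

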## Figures and Tables

**Table 1 pathogens-10-00812-t001:** Visit schedule.

	Screening Period (from −30 Days to Day 0)	Day 0	Population PK Day	Day 2 (Telephone Visit)	Month 3	Month 6
Informed consent	X					
Demographic and clinical information	X					
Concomitant medication	X	X	X	X		
Directed anamnesis	X	X	X	X	X	X
Physical examination	X	X	X		X	X
Ivermectin treatment		X				
Adverse events		X		X		
Full blood cell count	X			X ^a^	X	X
Biochemistry	X			X ^a^		
HIV serology	X					
*Loa loa* screening	X ^b^					
Coproparasitological study	X				X ^c^	X ^c^
Agar plate culture	X				X ^c^	X ^c^
*S. stercoralis* serology	X				X	X
*S. stercoralis* PCR	X				X	X
Serum and stool samples for repository		X			X	X
Plasma sample for PK		X	X			

^a^ In case of presenting relevant adverse events (at treating physician discretion). ^b^ In patients coming from endemic areas for *Loa loa*. ^c^ Only when they were positive at baseline.

## Data Availability

No new data were created or analyzed in this study. Data sharing is not applicable to this article.
